## Abstract

**Background:**

A pediatric cancer diagnosis and its treatment can have a detrimental effect on the mental health of children and their families. Screening to identify psychosocial risk in families has been recognized as a standard of care in pediatric oncology, but there has been limited clinical application of this standard thus far. A significant impediment to the implementation of psychosocial screening is the dearth of information on how to translate psychosocial screening to clinical practice, and specifically, how to follow-up from screening results. This manuscript aims to describe a protocol of a new intervention examining the feasibility and acceptability of mapping via a Psychosocial Navigator (PSN) psychosocial screening results to specific recommendations of resources for families based on measured risk for psychosocial distress and mental health symptoms.

**Methods:**

The pilot randomized control trial (RCT) consists of dyads of youth (10–17 years) newly diagnosed with cancer and their primary caregiver. This RCT includes two arms (intervention and control group), with each group completing measurements near diagnosis and 1 year later. After the initial assessment, dyads in the intervention group receive monthly screening results and recommendations from the study PSN that are tailored to these results. The patient’s primary healthcare team (nurse, social worker, oncologist) also receive the risk, distress, and mental health results as well as the recommendations from the PSN.

**Discussion:**

This study addresses a significant barrier to the implementation of psychosocial screening in pediatric oncology: specifically, the limited knowledge of how to follow-up from screening results. Findings from this pilot will inform a future definitive RCT to test the effectiveness of the intervention on patient and family mental health outcomes. This project has implications for enhancing clinical care in pediatric oncology, as well as other pediatric populations.

**Strengths and limitations of this study:**

This is the first study of screening and follow-up using a psychosocial navigator.

This study involves both patient and caregiver report.

The small sample size necessitates a future larger study to investigate the effects of intervention.

**Trial registration:**

NCT04132856, Registered 10 October 2019—retrospectively registered.

## Background

Approximately 300,000 children worldwide are diagnosed with cancer annually [1]. A pediatric cancer diagnosis and its treatment can have detrimental mental health effects on children/adolescents (youth) and their families, and subsequently on their quality of life [2, 3]. Youth diagnosed with cancer have more problems related to depression and anxiety than their healthy peers [4], and these symptoms are often present early in the diagnosis and treatment trajectory [5, 6]. Pre-teens and adolescents with cancer, in particular, have been identified as being at greater risk for mental health problems and reduced health-related quality of life [7, 8] and yet they have also been identified as an underserved group [9]. Caregivers of children diagnosed with cancer have been found to experience elevated symptoms of anxiety and depression, particularly near diagnosis and during the active treatment period [5, 10–12].

Of the 15 standards of psychosocial care in pediatric oncology [13], systematic psychosocial screening of families has received the greatest empirical support [14]. Early screening for psychosocial risk and mental health symptoms in youth with cancer and their family is an important first step for (1) identifying individuals and families who may be at risk for poor mental health and psychosocial adjustment; and (2) indicating a need for early psychological intervention and follow-up to prevent mental health impairments in this population [15]. The Psychosocial Assessment Tool (PAT) is an evidence-based instrument designed as a parent report measure for pediatric cancer and is grounded on the Pediatric Preventive Psychosocial Health Conceptual Model (PPPHM) of psychosocial risk (see Fig. 1) [16, 17]. Psychosocial risk is defined as “a constellation of individual, family, social, and economic factors that, when considered collectively, increase the likelihood that an individual or family members will experience difficulties in managing the challenges of cancer and its treatment” [18]. On the basis of the PPPHM, families are categorized into one of three risk levels: *universal*, representing the majority (~ 50–70%) of families who present minimal family risk factors and sufficient resources when facing childhood cancer; *targeted* families (~ 30%), who endorse some areas of risk and moderate resources, and, accordingly, may benefit from targeted (e.g., short-term, focused) interventions to assist with their adjustment; and finally, *clinical* families (~ 10–15%), who have more severe problems, many risk factors, few resources, and pre-existing mental health issues, and consequently likely require more intensive interventions to support their adjustment to pediatric cancer (see Fig. 1) [16, 17].

**Fig. 1 Fig1:**
[figure not shown]
The Pediatric Preventive Psychosocial Health Model (PPPHM)

Unfortunately, a limited number of pediatric institutions have implemented standardized psychosocial screening [19, 20] and even less evidence exists of the impact of psychosocial screening on patient and family outcomes [21]. The greatest impediment to the effective use of screening tools to assess psychosocial risk and distress in pediatric oncology remains the dearth of information on how to translate screening to clinical practice [22, 23]. Using the PAT, validated and adapted for the Canadian population [24], our team previously conducted a pilot *randomized controlled trial* (RCT) examining (a) the feasibility of conducting psychosocial screening in pediatric oncology using the PAT and providing a summary of the PAT to the child’s primary medical team, and (b) preliminary patient outcomes. Acceptability of PAT among providers was variable, with nurses reporting greater utility followed by oncologists and social workers reporting the lowest utility [25]. Child’s proxy pain-related quality of life (QOL) *(n*^*2*^
*= 0.08)* appeared to improve to a greater extent in the intervention compared to the control group [21]. After feedback from health care providers regarding the PAT summary and examining barriers to psychosocial screening [22], a larger (caregiver n = 122), definitive randomized controlled trial was conducted examining the effects of providing a psychosocial risk summary (revised) to the primary care team (oncologist, nurse, social worker) of a child newly diagnosed with cancer. Compared to the control group, improvements were seen over time in the intervention group on the patient proxy-reported QOL measure (*n*^*2*^
*= 0.87)* within the targeted/clinical risk subgroup [26]. As well, less depression symptoms were found in caregivers in the intervention group (d = .60) compared to the control group within the targeted/clinical risk [27]. Regardless of the group allocation, depression (d = .59) and anxiety symptoms (d = .47) declined over time for the caregivers; self-reported anxiety symptoms declined over time for siblings (d = .99), but neither depression nor anxiety self-reported symptoms declined over time in patients. Aside from the fact that the patient and sibling self-report samples were underpowered, these findings generally suggest that sharing early psychosocial risk screening results with the treating team is helpful but not enough to have a larger effect on mental health and quality of life outcomes in the family.

These previous studies [21, 24, 26, 27] were the foundation for the current pilot randomized control trial of an enhanced intervention. Specifically, the screening intervention was enhanced by including a psychosocial navigator with a unique role of communicating screening risk and mental health results initially and monthly for a year, tailoring resources recommendations to screening results, and communicating the screening information to both families and healthcare providers. We suspected these improvements may strengthen intervention impact on mental health and quality of life outcomes *in both* youth and the caregiver separately.

Further variables of interest will also be explored in this study, in order to determine outcomes to be further examined in a larger definitive RCT. Although coping strategies have not been examined in the context of psychosocial screening intervention, how people cope have been found to be critical for their psychosocial adjustment: primary control coping (e.g., problem solving, emotional modulation) and secondary control coping (e.g., acceptance, cognitive reappraisal) are associated with better psychosocial adjustment in caregivers of children diagnosed with cancer [28]. Thus, coping strategies are explored in this pilot study as potential mediators. Another important domain in the child’s life that is typically impacted by cancer diagnosis and treatment is social relations with friends and peers [29]. Thus, changes in social relations related to the intervention are also examined as exploratory outcomes. Finally, considering the well documented impact of childhood cancer treatment on the child fatigue level, sleep quality, and pain [30–32], these factors will also be explored as potential outcomes of this intervention. To summarize, this pilot RCT will inform if it is possible to conduct this enhanced screening intervention and which outcome variables appear to be related to the intervention. This information will be used for planning the future, definitive RCT evaluating the enhanced intervention with a large multi-center RCT.

## Aims and objectives

The purpose of this manuscript is three-fold: (a) to describe a comprehensive screening/intervention program called Enhanced Psychosocial Screening Intervention (EPSI), which was developed based on our previous work and feedback from health care providers and caregivers; (b) to conduct a pilot RCT to determine the feasibility and acceptability of EPSI to reduce caregiver and patient mental health symptoms and improve their quality of life. Primary outcomes are feasibility and acceptability of recruitment and data collection methods, acceptability of intervention components and delivery. Secondary outcomes are anxiety and depression symptoms and quality of life. Exploratory outcomes are measures of coping, social relationships, and physical outcomes (fatigue, sleep quality, and pain).

## Methods/design

### Study design

We use a parallel, randomized controlled pilot trial design with two study arms: the enhanced psychosocial intervention group (IG) and the treatment as usual control group (CG). Outcome assessments are conducted at baseline (2–6 weeks from diagnosis) and 12 months later (see Fig. 2 for timeline). Prior to the initiation of this study, we consulted with key stakeholders (community parents of children with cancer organization, oncologists, nurses, social workers, psychiatrists) regarding study design. We plan to continue to share outcomes of the study with stakeholders in order to foster continued engagement in psychosocial screening as a process.

**Fig. 2 Fig2:**
[figure not shown]
CONSORT flow chart

### Randomization

Upon completion of baseline measures, participants are randomly allocated at a 1:1 ratio to either the IG or CG. Using computer-generated numbers, the randomization is managed by the research coordinator for the project. The study coordinator maintains a double password-protected file with details of randomized allocation and reveals the randomization outcome to PSN after dyads complete consent procedures.

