### Participant inclusion criteria

The study is conducted with youth with cancer and one caregiver (primary caregiver). *Inclusion criteria for youth with cancer*: a new diagnosis of any type of cancer (within 4 weeks of diagnosis), between the ages of 10 and 17 years, medically suitable for participation (determined by the patient’s oncologist) and in active treatment (i.e., not palliative). Youth were excluded only if the treating clinical team thought a psychiatric or developmental disorder prevented them from active participation (e.g., completing assessment measures). *Inclusion criteria for caregiver*: primary caregiver of youth with cancer (as outlined above). Both youth with cancer and caregiver must agree to participate in the study. Given the culturally diverse population at HSC, families with limited English fluency but interested in participating are provided with translation services.

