### Feasibility and acceptability

Outcomes and endpoints for feasibility are measured by criteria of intervention acceptability; recruitment and retention; intervention satisfaction; and feasibility of completing outcome measures of intervention effectiveness.

Acceptability will be assessed using (a) estimates of recruitment, retention, and withdrawal rate; (b) estimates of completed assessment screenings, data collection procedures, and specific outcome measures; (c) in the intervention group, youth’ and parents’ perceptions of the acceptability of EPSI intervention, including their acceptability of monthly screening and feedback by the PSN, as well as their views about the intervention gathered during the end of intervention interview. Finally, (d) examination of treatment effects (e.g., effect sizes, variance measures/standard deviation) on secondary mental health and quality of life outcomes and exploratory variables will inform the selection of outcome measures for the future, definitive RCT.

*Intervention acceptability* is measured by participation in screening, assessment, and intervention activities (defined as treatment accepters when the participant completes all required measures and questionnaires). Recruitment and *retention* will be measured by (i) accrual and dropout rates; and (ii) proportion of completed questionnaires (defined as 100% when all measures completed at baseline and 12 months post-baseline). *Intervention satisfaction* will be measured by (i) comparing recruitment and retention between both groups; (ii) brief questionnaire completed by all caregivers and youth at the completion of study; and (iii) by the semi-structured interview completed by youth and caregivers who participate in the IG (Table 3). Finally, potential benefits of EPSI will be estimated comparing the secondary outcomes (mental health and quality of life) and exploratory outcomes (coping, social relationships, and physical functioning) in the IG and CG.

**Table 3 Tab3:** Semi-structured interview questions

1. **Thinking back to when you first agreed to participate in the study, what was it about the project that made you say “yes”?**	
2. **What was it like for you to participate in the study? (Tell us about your own experience?)**	
3. **What were your expectations about being in this study?**	
4. **How were your expectations met or not met? (Explain.)**	
5. **How did you find the experience with the Psychosocial Navigator?**	

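### The pooled comparison that selects outcomes for the definitive trial ignores baseline PAT risk tier and can understate effects in targeted/clinical families

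*Protocol article*

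**What the plan says.** **Allocation and eligibility.** Under Randomization: "Upon completion of baseline measures, participants are randomly allocated at a 1:1 ratio to either the IG or CG". No stratification factor is named. Youth qualify with "a new diagnosis of any type of cancer (within 4 weeks of diagnosis), between the ages of 10 and 17 years", and neither the inclusion nor the exclusion criteria refer to psychosocial risk tier.

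**Tier.** Table 2 lists the PAT as a baseline caregiver measure, so tier is known before allocation. Under Intervention (IG), resources are mapped to PAT tier together with anxiety and depression levels, and later to monthly distress. The Background describes the universal tier as "representing the majority (~ 50–70%) of families who present minimal family risk factors and sufficient resources when facing childhood cancer". It puts targeted families at about 30% and clinical families at about 10–15%.

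**Earlier evidence.** In the Background text after Fig. 1, the larger predecessor trial (122 caregivers) reports a proxy quality-of-life benefit within the targeted/clinical subgroup. For caregivers, "less depression symptoms were found in caregivers in the intervention group (d = .60) compared to the control group within the targeted/clinical risk". A smaller, earlier pilot reports a benefit on proxy pain-related quality of life with no tier restriction.

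**Comparison and use.** Under Feasibility and acceptability, "potential benefits of EPSI will be estimated comparing the secondary outcomes" and the exploratory outcomes between the two arms. Data analysis names t tests, which are to show which outcomes go forward to the multi-site trial. Neither section mentions tier.

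**The concern.** The article's main evidence of a between-arm benefit comes from the minority of families at raised risk. The pilot enrols every tier, and its stated comparison averages over them. If universal families have less to gain, an outcome that responds in at-risk families can look flat in the pooled contrast and be left out of the definitive trial. The variable needed to see this is collected before randomisation and already used to tailor the intervention, yet the stated comparison leaves it out.

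A second, smaller issue is chance imbalance. With about 20 dyads per arm and no stratification, the arms can differ noticeably in their number of at-risk families, and an unadjusted t test takes no account of that.

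**Working it through.** **The plan's own figure.** The sample size is 36–40 dyads, 18–20 per arm: 2 × 18 = 36 and 2 × 20 = 40. It rests on a cited pilot-trial recommendation. No power, effect size or SD is given, so there is no power calculation to reproduce.

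**Inputs.**
- Effect in targeted/clinical families: d = 0.60 (Background, caregiver depression).
- Universal share u: 0.50–0.70 (Background), so the targeted/clinical share is 0.30–0.50. The article's separate figures, 30% plus 10–15%, give 40–45%, inside that range.
- Effect in universal families: not given. I write it as k × 0.60 with k = 0, 0.5 or 1.
- Common SD of 1 (assumption).

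**Dilution.** Pooled d = 0.60 × (1 − u) + k × 0.60 × u.

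| k | u = 0.50 | u = 0.70 |
|---|---|---|
| 0 | 0.30 + 0 = 0.30 | 0.18 + 0 = 0.18 |
| 0.5 | 0.30 + 0.15 = 0.45 | 0.18 + 0.21 = 0.39 |
| 1 | 0.30 + 0.30 = 0.60 | 0.18 + 0.42 = 0.60 |

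**What the pilot t test would see.** At 20 per arm, two-sided 5%, noncentral t, power is 46% at d = 0.60, 15% at d = 0.30 and 9% at d = 0.18. A flat result is weak evidence even without dilution, and weaker still with it.

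**Chance imbalance.** Suppose 40 dyads are split 20/20 without stratification. The hypergeometric probability that the arms differ by four or more targeted/clinical families is 30.1% if there are 12 such families, 33.3% if 16 and 34.3% if 20.

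**Precision by tier.** The approximate 95% half-width for d is 1.96 × √(2/n), with n per arm.
- Pooled: n = 20 gives 0.62; n = 18 gives 0.65.
- Targeted/clinical: 40 × 0.30 to 0.50 = 12–20 dyads, or 6–10 per arm. n = 10 gives 0.88; n = 6 gives 1.13.
- At the article's 70% retention threshold, 28 of 40 dyads remain and 8.4–14 are targeted/clinical, about 4–7 per arm. n = 7 gives 1.05; n = 4 gives 1.39.

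**The case against.** **The zero effect in universal families is nowhere documented.** This stands. An unreported effect is not a null effect. The d = 0.60 also comes from a different intervention, a risk summary sent to the care team. EPSI adds a navigator, feedback to families and monthly distress screening, so a family in the universal tier at baseline can still receive more intensive recommendations. The result is therefore a range over k, which includes no dilution at all.

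**A reader might infer that earlier benefits were seen only in targeted/clinical families, or that tier is not used at all.** The article supports neither. The smaller pilot's benefit carries no tier restriction, and tier shapes the intervention group's recommendations. The gap is in the comparison of outcomes.

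**A reader might infer a 4- to 11-fold larger definitive trial.** At 80% power, two-sided 5%, about 44 per arm are needed at d = 0.60, against 175 at 0.30 and 485 at 0.18. That arithmetic is right but holds only for k = 0. It also ignores screening: finding 88 targeted/clinical families at 30–50% prevalence means screening about 176–293, against 350–970 all-comers, a ratio of about 2.0–3.3. And the article says that effect sizes will guide the selection of outcomes; it does not say that they will set the sample size.

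**The pooled effect may be the right planning value.** This stands if the definitive trial is also unselected, and no passage restricts it. The pooled estimate should therefore be kept.

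**Tier analyses may be in a fuller plan, and the primary outcomes are feasibility and acceptability.** Both are fair, and they limit the weight of the point. But the article does state the method by which outcomes are to be selected, and that method leaves out a variable that its own background evidence singles out.

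**Conclusion.** The point holds in a limited form. The stated pooled t test can understate effects in targeted/clinical families. Taking d = 0.60 there and 50–70% universal families, the pooled d is 0.18–0.30 with no universal effect, 0.39–0.45 with half, and 0.60 with the full effect. The 0.60 is for caregiver depression only and is borrowed from a different intervention, so these values illustrate and do not predict.

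The consequence falls on the choice of secondary and exploratory outcomes for the next trial, not on the pilot's primary objective. It does not show that enrolment should have been restricted by tier, or that the pooled estimate is wrong for an unselected definitive trial. It is worth acting on because the remedy uses data already collected.

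**What to change.** In Data analysis:

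1. Adjust the secondary and exploratory comparisons of the two arms for baseline PAT tier (universal versus targeted/clinical), for example with a linear model containing arm and tier. This deals with chance imbalance. It does not undo dilution, because the adjusted arm effect still averages over tiers.
2. Report effect sizes with 95% confidence intervals for each tier beside the pooled value, labelled descriptive. This is the step that makes dilution visible.
3. State that no outcome will be dropped from the definitive trial on the pooled t test alone.

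The cost is a few sentences and no new data. The downside is imprecision: about 6–10 targeted/clinical dyads per arm, with a half-width of roughly 0.9–1.1 SD, wider after dropout. The tier estimates should inform outcome choice and the discussion of eligibility, and should not decide either.

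Stratified allocation is not worth pursuing now: Trial status reports 38 dyads enrolled against a target of 36–40.

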### Blindness

A research assistant who is blinded to participant group allocation and study objectives scores outcome measures. Although healthcare providers (HCPs) caring for the child in the IG are not blinded to group allocation, HCPs in general are blinded to the identity of the participants in the CG.

### Study setting

Every year, approximately 600 youth are diagnosed with cancer in Ontario. Of these, approximately 60% of all pediatric oncology patients are treated at the Hospital for Sick Children (HSC), with an estimate of approximately 100 youth between the ages of 10 and 17 years. We aim to recruit approximately 40 dyads (one caregiver and youth) over a 16-month period.

As the largest pediatric academic health sciences center in Canada at the forefront of pediatric research and treatment, HSC is an ideal location to conduct this research project. Given the low incidence rate of pediatric cancer, the extensive catchment area served by HSC will be instrumental for recruitment of the necessary sample size. HSC provides a supportive, extensive research infrastructure including biostatistics, design, and analysis services. Additionally, within the oncology program, we have a collaborative well-established team of pediatric oncology clinician/researchers with rich psychosocial expertise.

